#### 1.4.9.2 Power calculation based on $P_{max}/kg$

A better endpoint would be power output per kilogram (P/kg) at a submaximal level, such as 80% of  $V_{O2,max}$ . Unfortunately no studies have been performed using this endpoint, so the effect of rHuEPO on P/kg at 80%  $V_{O2,max}$  is still unknown. The mean P/kg at 80%  $V_{O2,max}$  of 11 male professional cyclists however, is 5.2 W/kg with a standard deviation of 0.199.  Using a sample size of 22 (including 10% attrition rate) and a two-tailed t-test with a 0.05 two sided significance level a difference of 0.172 W/kg can be detected with a power of 80%. This difference would mean that a professional cyclist weighing 75 kg would go from an average of 390 W at 80%  $V_{O2,max}$  to 402.9 W. On a racing bike weighing 9 kg sitting in racing position at 25 degrees Celsius, this would produce a speed of 43.80 km/h and 44.32 km/h respectively (calculated from <http://bikecalculator.com>). In a flat terrain of 40 km this would result in a finish time of 54 min 48 sec and 54 min 09 sec, a difference of 39 seconds, which is very relevant in a race like to Tour the France.

## **2 STUDY OBJECTIVES**

### **2.1 Primary objective**

To explore the effects of NeoRecormon on cycling performance by

- performance in *exercise tests*
- measuring markers from the haematological module of the *Athlete Biological Passport*
- measuring *blood flow*

in well-trained cyclists.

### **2.2 Secondary objectives**

To explore the effects of NeoRecormon on cycling performance in a competition (road race)

To evaluate the safety of NeoRecormon in well-trained cyclists

To evaluate the performance of doping detection methods for NeoRecormon use in well-trained cyclists

### **2.3 Exploratory objectives**

To explore how a standardized submaximal exercise affects gene expression patterns in well-trained individuals.

To explore the difference in RNA-profiles between individuals treated with rHuEPO and placebo

To identify potential transcripts that can be used as biomarkers for rHuEPO use

To explore correlations between changes in whole blood gene expression patterns observed before and after a submaximal exercise test in individuals and their performance

### 3 STUDY DESIGN

#### 3.1 Overall study design and plan

This study will explore the effects of NeoRecormon on well-trained cyclists and their cycling performance during exercise tests and in a competition. It will consist of a screening, a training of the ramp exercise tests, 8 treatment visits, an 8 week training program, 7 exercise test visits, a competition and a follow-up visit which are outlined in the study Visit and Assessment Schedule (see Table 1).

The total duration of the study for each subject will be up to 129 days divided as follows:

| Study periods**                                    | Days*                                                                    |
|----------------------------------------------------|--------------------------------------------------------------------------|
| Screening + Training ramp exercise test            | -42 to -2 days                                                           |
| Ramp + TTE exercise test for baseline measurements | -7 to -1 days                                                            |
| Visit clinical unit: Treatment                     | 0/1/2, 7/8/9, 14/15/16, 21/22/23, 28/29/30, 35/36/37, 42/43/44, 49/50/51 |
| Visit clinical unit: Ramp exercise tests           | 11/12/13/14, 25/26/27/28, 39/40/41/42, 53/54/55/56                       |
| Visit clinical unit: TTE exercise test             | 46/47/48/49                                                              |
| Training                                           | 0 to 55                                                                  |
| Competition                                        | 57 to 60                                                                 |
| Follow-up                                          | 80 +- 7                                                                  |

\* / means 'or'

\*\* TTE = Time to exhaustion

Dosage is spread over three days because it is logistically very difficult to perform safety measurements in 48 subjects and inject them afterwards with the study drug in one day. The exercise tests are spread over four days for the same reason.

##### 3.1.1 Screening

The screening phase (days -42 to -2) will only be started after full written, verbal and signed informed consent has been obtained, according to CHDR standard operating procedures. The entire screening process will last approximately 2 hours. The screening will be divided into two parts:

##### Medical screening

- Medical interview
- Physical examination
- 12-lead ECG
- Vital signs (Heart rate, blood pressure)
- Weight
- Height
- Urine Drug Screen (THC, morphine, benzodiazepines, cocaine, amphetamines, methamphetamines, MDMA)
- Alcohol Breath Test
- Blood sampling (haematology, biochemistry, serology, coagulation)
- Urinalysis

##### Training

- Exercise test performed on an ergometer (see Appendix 5 – Exercise test for a more detailed description)

During screening urine and blood samples will be collected from each patient for analysis as

described in section 7.2.6.

### **3.1.2 Treatment and exercise tests**

The time schedule of study days is provided in general in the Visit and Assessment Schedule (see Table 1). On treatment days subjects will arrive at the clinical unit at a predetermined time. Before dosing standard safety measurements will be performed (see Table 1).

Subjects will perform a ramp exercise test every two weeks during the treatment period. They also will perform a Time To Exhaustion exercise test in the 7th treatment week. Baseline measurements for these tests will be performed 2 weeks prior to the treatment period. During the exercise test maximal and submaximal exercise parameters will be measured. Before and during the exercise tests blood will be collected at predetermined stages.

### **3.1.3 Training period**

During the treatment period (8 weeks) subjects will maintain their usual training programme. They will record their training intensity during this period in a diary. Additionally, subjects bikes will be mounted with a Pioneer power meter that will be used for each training activity to log the trip. This information will be shared with the investigators.

### **3.1.4 Competition**

After the treatment period subjects will participate in a competition. The competition is designed in a way that it closely resembles real racing conditions and complies with the required performance duration. During the competition physiological parameters will be measured. Before and after the competition blood will be collected at predetermined stages.

Please refer to appendix 6 for a detailed description of the competition.

### **3.1.5 Follow-up**

A follow-up visit will be performed 30 days after the last visit, which includes a final physical examination, safety laboratory tests (haematology, chemistry, coagulation and urinalysis) and the measurement of vital signs (see Visit and Assessment Schedule, Table 1). Subjects will also be asked if they believe they were on active or placebo treatment. A description of all procedures and analyses is included in section 7.2.

### **3.1.6 Urine doping control**

Urine will be collected at two predetermined periods. In the second treatment week samples will be taken pre-dose (day 7/8/9), two days later (day 9/10/11), at day 11/12/13/14 before and after the exercise test and pre-dose at day 14/15/16. Additionally, one sample will be taken before and after the competition (week 9). These samples will be sent to a lab (DoCoLab – Ugent, [name]) specialized in rHuEPO (NeoRecormon) detection in urine, according to the current protocol of the Dutch Doping Authority.

Please refer to appendix 7 for a detailed description of the urine doping control procedure.

## 4 STUDY POPULATION

### 4.1 Subject population

A total of 48 subjects will be enrolled into the study following satisfactory completion of a screening visit where eligibility for the study will be checked. Subjects will be recruited via media advertisements and via advertisements at cycling associations.

### 4.2 Inclusion criteria

Eligible subjects must meet all of the following inclusion criteria:

- ❖ Well-trained (as determined by cycling history and maximal power output  $>4$  W/kg) male subjects, 18 to 50 years old (inclusive);
- ❖ Subjects must be healthy / medically stable on the basis of clinical laboratory tests, medical history, vital signs, and 12-lead ECG performed at screening, including exercise ECG.
- ❖ Each subject must sign an informed consent form prior to the study. This means the subject understands the purpose of and procedures required for the study.

### 4.3 Exclusion criteria

Eligible subjects must meet none of the following exclusion criteria:

- ❖ Any clinically significant abnormality, as determined by medical history taking and physical examinations, obtained during the screening visit that in the opinion of the investigator would interfere with the study objectives or compromise subject safety.
- ❖ Unacceptable known concomitant diagnoses or diseases at baseline, e.g., known cardiovascular, pulmonary, muscle, metabolic or haematological disease, renal or liver dysfunction, ECG or laboratory abnormalities, etc.
- ❖ Unacceptable concomitant medications at baseline, e.g., drugs known or likely to interact with the study drugs or study assessments.
- ❖ Unacceptable potential cycling performance enhancing medications at baseline, e.g. Erythropoiesis-stimulating agents, Anabolic Androgenic Steroids, Growth Hormone, Insulin, IGF-I and Beta-Adrenergic Agents.
- ❖ Blood transfusion in the past three months.
- ❖ Loss or donation of blood over 500 mL within three months.
- ❖ Participation in a clinical trial within 90 days of screening or more than 4 times in the previous year.
- ❖ Known hypersensitivity to the treatment or drugs of the same class, or any of their excipients.
- ❖ Any known factor, condition, or disease that might interfere with treatment compliance, study conduct or interpretation of the results such as drug or alcohol dependence or psychiatric disease.
- ❖ Positive urine drug test at screening.
- ❖ Positive alcohol breath test at screening.
- ❖ Haemoglobin (Hb) concentration  $> 9.8$  mmol/l at screening.
- ❖ Hb concentration  $< 8$  mmol/l at screening.
- ❖ Haematocrit (Ht)  $\geq 48\%$  at screening.

- ❖ Being subject to WADA's anti-doping rules, meaning being a member of an official cycling union or other sports union for competition (such as the KNUU) or participating in official competition during the study.
- ❖ Positive results from serology at screening (except for vaccinated subjects or subjects with past but resolved hepatitis)
- ❖ Previous history of fainting, collapse, syncope, orthostatic hypotension, or vasovagal reactions.
- ❖ Any circumstances or conditions, which, in the opinion of the investigator, may affect full participation in the study or compliance with the protocol.

#### **4.4 Concomitant medications**

The clinical results obtained so far do not indicate any interaction of NeoRecormon with other medicinal products.

All medications (prescription and over-the-counter [OTC]) taken after study screening until the end of the study will be recorded.

##### **4.4.1 Mandatory concomitant supplementation**

Mandatory concomitant supplementation for all 48 subjects:

- ❖ 50mg vitamin C (ascorbic acid) per day
- ❖ 200 mg iron (ferrofumarate) per day

##### **4.4.2 Allowed concomitant medications**

Allowed concomitant medications:

- ❖ Paracetamol
- ❖ Other medications are only allowed if they are discussed, approved and clearly documented by the investigator.

##### **4.4.3 Prohibited concomitant medications**

Prohibited concomitant medications:

- ❖ All substances (except NeoRecormon during treatment period) that enhance cycling performance are prohibited within 6 months prior to study drug administration and during the course of the study (e.g. Other Erythropoiesis-stimulating agents, Anabolic Androgenic Steroids, Growth Hormone, Insulin, IGF-I and Beta-Adrenergic Agents etc.).

#### **4.5 Lifestyle restrictions**

In the interest of the subjects' safety and to facilitate assessment of the treatment effect, the patients participating in this study will be requested to agree to the following restrictions during the study:

- Alcohol will not be allowed from at least 24 hours before screening and before each scheduled visit, and whilst in the study unit until discharge from the study unit.

- During the study subjects are not allowed to be subject to WADA's anti-doping rules, meaning they are for example not allowed to be a member of an official cycling union or other sports union for competition (such as the KNWU). NeoRecormon treated subjects are not allowed to become a member of such a union for 3 months after the last dose.
- Subjects must maintain their usual training programme until the end of the treatment period (week 1-8). They will record their training activity in a diary and using the Pioneer power meter. Directly after the treatment period (week 9) the subjects will participate in a competition (see appendix 6).

## **4.6 Study drug discontinuation and withdrawal**

### **4.6.1 Study drug interruption or discontinuation**

The investigator must temporally interrupt or permanently discontinue the study drug if continued administration of the study drug is believed to be contrary to the best interests of the subject. The interruption or premature discontinuation of study drug might be triggered by an Adverse Event (AE), a diagnostic or therapeutic procedure, an abnormal assessment (e.g., ECG or laboratory abnormalities), or for administrative reasons in particular withdrawal of the subject's consent. The reason for study drug interruption or premature discontinuation must be documented.

### **4.6.2 Subject withdrawal**

Subjects have the right to withdraw from the study at any time for any reason. Should a subject decide to withdraw from the study, all efforts should be made to complete and report the observations, particularly the follow-up examinations, as thoroughly as possible.

### **4.6.3 Replacement policy**

Subjects withdrawing in the first treatment week for reasons other than adverse events or any other tolerability issues with the treatment will be replaced.

## **5 INVESTIGATIONAL MEDICINAL PRODUCT**

### **5.1 Investigational drug and matching placebo**

Study drug or placebo will be administered to the subjects as detailed in Table 1. NeoRecormon will be ordered as available and its matching placebo will be manufactured. The investigational drug and its matching placebo are indistinguishable and will be packaged in the same way. Blinding will be accomplished by using the same syringes or by covering the syringes with aluminum foil.

### **5.2 Comparative drug**

Placebo: Saline, 0.90% w/v NaCl.

### **5.3 Study drug dosing scheme**

Please refer to Figure 1 for a detailed dosing schedule.

### **5.4 Study drug packaging and labelling**

NeoRecormon and placebo will be acquired, packaged and labelled by the LUMC pharmacy in accordance with local regulations. Upon arrival at the pharmacy, the investigational products should be checked for damage and verify proper identity, quantity, integrity of seals and temperature conditions, and report any deviations or product complaints upon discovery. The dispensing of the study drug will be performed by the pharmacy. Study drug will be dispensed for each subject according to the randomization list. Study drug packaging will be overseen by the Leiden University Medical Centre Pharmacy and bearing a label with the identification required by local law, the protocol number, drug identification, and dosage.

All subcutaneously administered drugs and placebos will be indistinguishable and will be packaged in the same way.

The study drug must be stored between 2°C and 8°C in a secure, temperature-controlled (refrigerator) area with limited access. The vial must be kept in the outer carton, in order to protect it from light.

For the purpose of ambulatory use, the unreconstituted product may be removed from the refrigerator and be stored at room temperature (not above 25°C ) for one single period of up to 3 days. Leaving the reconstituted solution outside the refrigerator should be limited to the time necessary for preparing the injections.

### **5.5 Drug accountability**

Drug accountability will be maintained by the Leiden University Medical Centre Pharmacy and assessed by maintaining adequate study drug dispensing records.

The investigator is responsible for ensuring that dosing is administered in compliance with the protocol. Delegation of this task must be clearly documented and approved by the investigator. All study drug administration will occur under medical supervision.

### **5.6 Treatment assignment and blinding**

#### **5.6.1 Treatment assignment**

Subjects must be randomized in a consecutive order starting with the lowest number. Replacement subjects will be numbered +100, e.g. subject 5 will have subject 105 as replacement, and subject 105 will have subject 205 as replacement, etc.

The randomization code will be generated SAS version 9.1.3 (or a more recent version, if available) by a study-independent, CHDR statistician. To reduce the variability between active and placebo,

block randomisation will be used, with one block of subjects aged 18-34 (inclusive) and another of subjects aged 34-50 (inclusive). The sample size of the blocks will be determined at day -14, when the included subjects have been identified. An attempt will be made to choose the highest block size. The randomization code will be unblinded/broken and made available for data analysis only after study closure, i.e., when the study has been completed, the protocol deviations determined, and the clinical database declared complete, accurate and locked. The randomization code will be kept strictly confidential. Sealed individual randomization codes, per subject and per treatment, will be placed in a sealed envelope containing the and labelled 'emergency decoding envelopes' will be kept in a safe cabinet at CHDR.

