#### 7. Subjects / Groups

A total of 48 subjects are planned to be enrolled in this study. Eligible subjects will be randomized to the NeoRecormon or Placebo treatment groups on a 1:1 basis.

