## 9.9 Efficacy endpoints

### 9.9.1 Efficacy

The final analysis will be preceded by a blind data review which consists of individual graphs per visit by time of all efficacy measurements by time. The graphs will be used to detect outliers and measurements unsuitable for analysis. The efficacy parameters will be listed by treatment, subject, visit and time. Individual graphs by time will be generated.

All measured PD endpoints will be summarised (n, mean, SD, SEM, median, Min and Max values) by treatment and time, and will also be presented graphically as mean over time, with standard deviation as error bars. All efficacy endpoints will be summarised (mean, SD, SEM, median, Min and Max values) by treatment, and will also be presented graphically as mean in a bargraph, with standard deviation as error bars.

Parameters will initially be analyzed without transformation, but if the data suggest otherwise, log-transformation may be applied. Log-transformed parameters will be back-transformed after analysis where the results may be interpreted as percentage change.

To establish whether significant treatment effects can be detected on the measured efficacy parameters, each parameter that is measured repeatedly will be analyzed with a mixed model analysis of covariance (ANCOVA) with treatment, time and treatment by time as fixed factors and subject, subject by treatment and subject by time as random factors and the (average) baseline measurement as covariate. Parameters that are only measured at baseline and at the end of the treatment phase will be analysed with a one-way ANCOVA with treatment and baseline as covariate.

Single measured efficacy parameters will be analyzed with an unpaired t-test.

The Kenward-Roger approximation will be used to estimate denominator degrees of freedom and model parameters will be estimated using the restricted maximum likelihood method.

The general treatment effect and specific contrasts will be reported with the estimated difference and the 95% confidence interval, the least square mean estimates and the p-value. Graphs of the Least Squares Means (LSM) estimates over time by treatment will be presented with 95% confidence intervals as error bars, as well as change from baseline LSM estimates.

The following contrasts will be calculated within the model:

- NeoRecormon - Placebo

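### The two age strata for randomisation overlap at 34 years, and no listed efficacy model includes the stratum, so the list is not uniquely defined and some precision may be lost

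*Protocol*

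**What the plan says.** Section 5.6.1 gives the aim of the age blocks as "To reduce the variability between active and placebo" and defines them "with one block of subjects aged 18-34 (inclusive) and another of subjects aged 34-50 (inclusive". The two blocks act as strata. On their size it says "The sample size of the blocks will be determined at day -14, when the included subjects have been identified", and it prefers the largest block size possible. The list is made by a statistician independent of the study.

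Section 4.2 admits "male subjects, 18 to 50 years old (inclusive", so a man of 34 is eligible. Synopsis section 7 states "A total of 48 subjects are planned to be enrolled in this study" and "Eligible subjects will be randomized to the NeoRecormon or Placebo treatment groups on a 1:1 basis".

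The efficacy analyses are set out in three places:

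- **Section 9.9.1, repeated outcomes:** a mixed model with fixed effects for arm, time and their interaction, plus "subject, subject by treatment and subject by time as random factors and the (average) baseline measurement as covariate".
- **Section 9.9.1, outcomes taken at baseline and end of treatment:** a one-way ANCOVA on arm and baseline value.
- **Section 9.9.1, outcomes taken once:** "Single measured efficacy parameters will be analyzed with an unpaired t-test".
- **Synopsis section 19:** a mixed model and ANCOVA of the same kind.
- **Appendix 5, statistics:** a repeated-measures ANOVA by group, followed by t-tests.

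None of them has a term for age or age stratum.

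**The concern.** There are two linked defects.

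1. **The strata are not a partition.** Age 34 lies in both bands, and nothing elsewhere in the protocol says which one applies. Block sizes are derived from the stratum counts at day -14, so the specification does not yield one list. Two statisticians following Section 5.6.1 could correctly build different lists from the same 48 men.

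2. **The stratum is used in the design but not in the analysis.** Forcing the arms to be alike on age makes the treatment estimate less variable if age is prognostic. A model without the stratum leaves the between-stratum variance in its error term, so its standard error does not reflect that gain. Intervals are then wider than they need be and the true type I error falls below 5%. In a trial of 48 subjects this is worth avoiding.

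**Working it through.** The protocol states no figure on this point, so there is none to reproduce.

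**Inputs from the protocol.** N = 48, 1:1, so 24 per arm; eligible ages 18 to 50; bands 18-34 and 34-50, both inclusive; two-sided alpha 0.05. For the power illustration, difference 1.5 ml/min/kg and SD 1.95 (Section 1.4.9.1).

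**Assumptions, not in the protocol.** Ages uniform over the eligible range (step 1 only), and R², the share of outcome variance explained by the stratum (steps 3 and 4).

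**Step 1: how many men the overlap touches.** Ages 18 to 50 are 50 − 18 + 1 = 33 single years. The expected number aged 34 is 48/33 = 1.45. The chance of at least one is 1 − (32/33)^48 = 0.77.

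**Step 2: effect on the list.** Moving one 34-year-old changes both stratum sizes by one. For example, strata of 24 and 24 become 23 and 25, and neither of those can be split equally between the arms.

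**Step 3: interval width.** With the arms balanced within strata, a comparison that omits the stratum reports an interval wider than the adjusted one by a factor of about 1/√(1 − R²):

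- R² = 0: 1.00
- R² = 0.05: 1/√0.95 = 1.026
- R² = 0.10: 1/√0.90 = 1.054
- R² = 0.20: 1/√0.80 = 1.118
- R² = 0.30: 1/√0.70 = 1.195

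**Step 4: simulation.** There were 40,000 runs per scenario, 24 per arm, strata split 50:50 and balanced 1:1 within stratum. The unadjusted two-sample t-test was compared with a linear model of treatment plus stratum. The SE ratio is the mean SE reported by the t-test divided by the actual spread of the estimate.

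| R² | SE ratio, t-test | Type I error, t-test | Type I error, with stratum | Power, t-test | Power, with stratum |
|---|---|---|---|---|---|
| 0 | 0.99 | 0.050 | 0.051 | 74.1% | 74.0% |
| 0.05 | 1.02 | 0.044 | 0.050 | 74.5% | 76.1% |
| 0.10 | 1.05 | 0.039 | 0.050 | 75.2% | 78.6% |
| 0.20 | 1.12 | 0.028 | 0.050 | 76.4% | 83.3% |
| 0.30 | 1.20 | 0.020 | 0.050 | 77.8% | 87.9% |

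A 25:75 split gives nearly the same (at R² = 0.20, SE ratio 1.12 and power 75.9% against 82.8%). Power of the unadjusted test rises a little with R² because the balanced estimate really is less variable; the test simply does not take credit for most of that gain. At R² = 0 the extra term costs nothing noticeable.

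The 74% at R² = 0 agrees with the exact two-sided t-test power of 74.2% for 24 per arm. That it lies below 80% is a separate question about the sample size and does not bear on this point.

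**Step 5: where the range applies.** The simulation has no baseline covariate, so it describes outcomes measured once, such as total race time (Section 6.1). For models that adjust for the subject's own baseline, the relevant R² is what the stratum still explains after baseline, which should be smaller.

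**The case against.** The overlap looks like a boundary slip. It affects a single year of age, perhaps one or two men. The loss of precision exists only if age predicts outcome, which the protocol does not show; at R² = 0 there is none. The exercise-test outcomes that carry the primary objective are adjusted for baseline, which should absorb much of any stable age effect, and the race is a secondary objective. Omitting the stratum errs on the conservative side in a trial whose efficacy aims are worded as exploration. Section 9.1 leaves full details to an SAP, which is not at hand and could add the term. Most of this stands and limits the weight of the point. The last argument does not remove it: the protocol lists its model terms in three places, and the stratum is in none of them.

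A reader might infer more in two respects, and the protocol does not support either:

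- **That staff could steer a 34-year-old to an arm.** Section 5.6.1 does not say who assigns the stratum. The list comes from a statistician independent of the study, and Section 5.6.2 withholds it from the investigator, study staff, subjects and monitors. Choosing a stratum does not choose an arm, and assignment is random in either.
- **That the purpose of the blocks is defeated.** Their stated aim is most naturally read as making the arms alike on age. Blocking does that whatever model follows, and the point estimate keeps the benefit. What may be lost is precision in the reported standard error.

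**Conclusion.** The point holds, and it is modest. The strata in Section 5.6.1 overlap at age 34, so stratum sizes and the randomisation list are not uniquely defined; this causes no bias. The efficacy models omit the stratum. If age is prognostic, confidence intervals are about 3, 5, 12 or 20% wider than needed at an assumed stratum R² of 0.05, 0.10, 0.20 or 0.30, and no wider at R² = 0. In the illustration the power given up is about 3 points at R² = 0.10 (78.6 − 75.2) and 7 points at 0.20 (83.3 − 76.4). These figures rest on the assumed R² and on an analysis without a baseline covariate. They therefore apply chiefly to single-measurement race outcomes, and less to the baseline-adjusted ones. The planned tests remain valid but may be conservative.

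**What to change.** 1. In Section 5.6.1, make the age bands non-overlapping, for example 18-34 and 35-50, before the list is generated. This changes one character.
2. In Section 9.9.1, Synopsis section 19 and Appendix 5, add age stratum as a fixed factor to the efficacy models.
3. For outcomes measured once, replace the unpaired t-test with a linear model of treatment plus age stratum.

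The cost is one degree of freedom (46 to 45 in a two-group comparison of 48 subjects), with no material loss of power even if age is unrelated to outcome (74.1% against 74.0%). Section 10.6.1 classes changes to the statistical analyses as non-substantial, so the model change carries little administrative burden.
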